### Serious adverse events

We expect a very low risk for participants. We do not foresee any serious adverse events. However, if participants do experience an adverse event, this will be brought immediately to the attention of the clinical staff. All participants will be monitored to prevent any possible deficiency or inadequate nutrient and/or caloric intake by means of an evaluation of their dietary intake (dietary recalls and/or food diaries). Participants will also be monitored for injuries or problems associated with increased physical activity.

### Statistical considerations

The present study is designed as a mono-institutional, randomized, controlled four-arm parallel-group trial. The study will be conducted over a 2-year period, during which patients will receive a 6-month intervention, and will be followed until the end of the study period. Study participants will be randomized to one of the four arms: Dietary Intervention (DI); Physical Activity Intervention (PAI); Physical Activity And Dietary Intervention (PADI); or Less Intensive Intervention (LII). The less intensive (or minimal) intervention group will be considered as the control group.

This design is chosen because it has the advantage of testing single or combined interventions, and of comparing the results with the control group (LII).

The mono-institutional study design will be characterized by uniform diagnostic procedures, standard treatment protocols and central pathological evaluation of surgical specimens, thereby limiting variations in the determination of major clinical and pathological factors that determine disease outcome. It will also ensure a uniform follow-up of patients for the study-specific endpoint.

The primary outcome measure will be assessed at the end of the 6-month intervention, by measuring the body weight. We expect a body weight reduction ≥5 % of the baseline body weight in all the intervention arms. The secondary outcome measures will be assessed through the intervention during the follow-up visits: (a) we expect weight control over the study period, measuring the body weight at each follow-up visit; (b) we expect an increase in physical activity levels and reduction in physical inactivity from baseline measured by the pedometer-like devices and from the IPAQ questionnaire. The physical activity target for improving general health is 30 minutes of moderate-to-vigorous intensity every day (equivalent to 10 MET-hours per week) and reducing inactivity; (c) we expect a change in dietary intake and an increased adherence to healthy diet from baseline using the FFQ; (d) we will evaluate the effect of the intervention on long-term breast cancer recurrence; (e) we expect an improvement in quality of life and in health status from baseline using the FACT-B and STAI; (f) we will evaluate the effect of intervention on the blood lipid profile. We expect an increase in HDL cholesterol and a decrease in LDL cholesterol, triglycerides and total cholesterol; (g) we will evaluate the effect of intervention on some biomarkers: estradiol, CRP, insulin, and glucose. Statistical analyses will only be carried out after the end of the trial, with no interim analysis planned.

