### Study outcomes

The main aim of the study is to evaluate the impact of a 6-month intervention program on body weight change (weight loss ≥5 % of the baseline body weight) in overweight or obese breast cancer survivors.

As secondary outcomes, we will further examine the impact of the intervention on long-term weight control or maintenance, physical activity and inactivity levels, dietary intake, health status, and quality of life. We will also examine the effect of intervention on blood lipid profile [total, high-density lipoprotein (HDL), low-density lipoprotein (LDL) and very low density lipoprotein (VLDL) cholesterol and triglycerides] and on estradiol, C-reactive protein (CRP), insulin, and glucose at 6-, 12- and 24-month visits.

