### Intervention

The principal aim of the intervention is to promote weight loss through diet and physical activity alone or in combination. The target goal is a 5 % weight loss 6 months after randomization. Participants will be followed up for a further 18 months and secondary outcome assessments will be made at 12 and 24 months (Table 1).

**Table 1 Tab1:** Study assessments

Assessments	Instrument	Visits			
		Baseline	6-month	12-month	24-month
Total, HDL, LDL and VLDL cholesterol, triglycerides, estradiol, insulin, glucose and C-reactive protein	Blood test	√	√		√
Height^a^, weight, waist and hip circumference, body mass index, waist-to-hip ratio	Calibrated scales, stadiometer, tape measure	√	√	√	√
Body composition (including total body water (TBW), body cell mass (BCM), extracellular water (ECW), fat-free mass (FFM), fat mass (FM) and percentage fat mass (% FM)	Bioelectrical impedance vector analysis (BIVA) (Nutrilab device, AKERN Srl – Italy)	√	√	√	√
Dietary target	24 hr recalls and/or food diary	√^b^	√		
Steps	Pedometer-like device	√^b^	√		
Diet	Food Frequency Questionnaire (FFQ)	√	√		√
Quality of life	Functional Assessment of Cancer Therapy- Breast (FACT-B)	√	√		√
Mood	State-Trait Anxiety Inventory (STAI)	√	√		√
Physical activity	International Physical Activity Questionnaire (IPAQ)	√	√		√

^a^Height will be assessed only at baseline

^b^24 hr recalls and/or food diary and the pedometer-like device will be used during the intervention to monitor individualized goals

Baseline assessment will be made for all participating women, prior to randomization in one of the four intervention arms (DI, PAI, PADI, and LII). All participants must wear the wrist-based activity monitor during the 6-month intervention period (day and night).

Participants randomized to one of the three intervention arms (DI, PAI, and PADI) will be given individualized counseling based on their lifestyle habits to reduce their weight. The motivational interviewing approach will be used to discuss behavior change that fosters a constructive specialist-patient relationship which could lead to better body weight control for the patients.

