### LII arm

Participants included in the LII arm will be considered as the control group. They will receive general counseling on health to reduce weight, and be provided with materials and guidelines available to the general public [4, 34, 35] and receive two motivational phone calls.

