### Sample size

During 2012, 756 overweight or obese women (with a BMI comprising between 25 and 40 kg/m^2^) underwent surgery for early-stage (non-metastatic) breast cancer at the European Institute of Oncology. Data for these patients were retrieved from our institutional breast cancer patients’ database. The mean weight of these 756 patients was 75 kg and the standard deviation was 9.

The sample size calculation was based on a superiority design of any single intervention (DI, PAI, or PADI) compared to the control group (LII). A sample group of 65 patients (control group) and similar number in any of the three intervention groups (diet and/or exercise) for a total of 195 patients achieve 80 % power to detect a 5 % weight loss (3.75 kg) between the null hypothesis that both group means are 75 kg and the alternative hypothesis that the mean of any of the intervention group 2 is 71.25 after 6 months, with known group standard deviations of 9.0 and 9.0 and with a significance level (alpha) of 0.05 using a two-sided two-sample *t* test. We have foreseen a drop-out of 5 % over the first 6 months.

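### The 5 % target is a loss from baseline in the aims but a difference from control in the sample size; at the planned means these agree only if the counselled control arm does not change

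*Protocol article*

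**What the plan says.** Three sections state the target without a comparator. Study outcomes gives the main aim as the programme's impact on "body weight change (weight loss ≥5 % of the baseline body weight) in overweight or obese breast cancer survivors". The Intervention section says "The target goal is a 5 % weight loss 6 months after randomization". Statistical considerations, on the primary outcome, says "We expect a body weight reduction ≥5 % of the baseline body weight in all the intervention arms".

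The Sample size section makes the comparison between arms: "The sample size calculation was based on a superiority design of any single intervention (DI, PAI, or PADI) compared to the control group (LII"). Its stated purpose is "to detect a 5 % weight loss (3.75 kg) between the null hypothesis that both group means are 75 kg". Against this, it places an intervention arm at 71.25 kg by 6 months. The control mean for that scenario is not given separately, so it stays at 75 kg. That figure is also the mean weight of the 2012 institutional series from which the inputs were taken.

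The LII arm is a reduced intervention. Of its participants the article says: "They will receive general counseling on health to reduce weight, and be provided with materials and guidelines available to the general public". They also receive two motivational phone calls, and the Intervention and Measures sections have every participant wear the activity monitor for the 6 months.

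Statistical methods lists the t test, ANCOVA and multiple linear regression for changes in means before and after the intervention. That sentence does not name the contrast with LII.

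**The concern.** One figure, 5 % or 3.75 kg, serves for two quantities: how far an intervention arm falls below its own starting weight, and how far it ends below LII. They differ by whatever LII does over 6 months. The sample size calculation sets that change to zero without saying so, for an arm given advice to lose weight, two motivational calls and an activity monitor.

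Two things are at stake. First, an arm could lose exactly 5 %, as expected, while its difference from LII is smaller than the one the trial is sized to detect. Second, the before-and-after wording in Statistical methods, together with a target set from baseline, leaves room to present a within-arm loss as the primary result. Only the contrast with LII is randomised evidence; a loss that LII partly shares is not an effect of the intervention.

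**Working it through.** **Inputs, all from the Sample size section:** baseline mean 75 kg; intervention mean 71.25 kg at 6 months; SD 9.0 in each group; two-sided alpha 0.05; two-sample t test; 65 per group; stated power 80 %; 5 % drop-out by 6 months. The LII change is not in the article and is varied below as an assumption.

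**Step 1. Where the two definitions meet.** 5 % of 75 kg is 0.05 × 75 = 3.75 kg, and 75 − 3.75 = 71.25 kg. If the intervention arm loses 5 % and LII loses c %, then

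difference = 0.75 × (5 − c) kg.

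This equals 3.75 kg only at c = 0. To keep 3.75 kg when LII loses 2 %, the intervention arm must lose 7 %, i.e. 5.25 kg.

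**Step 2. The article's own power figure.** The standard error of the difference is 9 × √(2/65) = 1.579 kg. The noncentrality is 3.75 / 1.579 = 2.375, which gives power of 65.5 % by the noncentral t (66.1 % by the normal approximation). With 62 per arm after drop-out it is 63.4 %. The stated 80 % is therefore not reproduced for one arm against LII; that would take about 91 per arm (normal approximation). The figures 65 and 195 do reproduce as LII against the three intervention arms pooled: 61 controls are needed at 3:1, 61 / 0.95 rounds up to 65, and power at 65 v 195 is 82.6 %. The text, however, describes a single-arm comparison. This shortfall arises at zero LII change and is a separate error.

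**Step 3. Vary the LII change, holding the intervention arm at a 5 % loss.** Power by the noncentral t, unadjusted, SD 9:

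| Mean LII change (assumed) | Difference | Power, 65 v 65 | Power, 65 v 195 pooled |
|---|---|---|---|
| gain of 1 % | 4.50 kg | 81 % | 94 % |
| none | 3.75 kg | 65 % | 83 % |
| loss of 1 % | 3.00 kg | 47 % | 64 % |
| loss of 2 % | 2.25 kg | 29 % | 41 % |

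Only the movement away from the row with no change belongs to this point.

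**Step 4. Baseline adjustment.** ANCOVA on baseline weight reduces the SD to about 9 × √(1 − r²). The article gives no correlation r between baseline and 6-month weight. If r = 0.8, the SD is 5.4 kg, and power at 65 v 65 is about 98 % for 3.75 kg and 65 % for 2.25 kg. If r = 0.9, the SD is 3.9 kg, and power for 2.25 kg is about 90 %. The level rises, but power still depends on the LII change.

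**The case against.** The strongest reply is that nothing here is contradictory. The expectation is a loss of at least 5 %, which is a floor. With a 7 % loss in the intervention arm and 2 % in LII, both statements hold. That stands, and a reader who infers a strict contradiction goes too far. It does not remove the point, because the Sample size section fixes the intervention mean at 71.25 kg, exactly 5 % below 75 kg. At those planned values zero LII change is required.

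A reader might also infer that the trial means to judge efficacy by a within-arm loss. The article does not say so. Statistical considerations, Sample size and Discussion all name LII as the comparator, and the 5 % in the Intervention section reads as a behavioural goal. What remains is looseness: the primary expectation is stated without a comparator, and the methods sentence speaks of before and after.

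Third, zero LII change may be reasonable. The Background reports that most women gain weight during and after treatment, and LII receives only public materials and limited contact. A gain in LII would widen the difference. Eligible women completed their main treatment more than 6 months earlier, so the first-year gains quoted there do not carry over directly. The article does not settle the direction, and it does not support a claim that LII will lose weight.

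Finally, reading the whole fall from 80 % to 29 % as the effect of a 2 % LII loss would be wrong. The part from 80 % to about 65 % occurs at zero LII change. The low figures also rest on an unadjusted SD of 9, although ANCOVA is listed.

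**Conclusion.** The point holds as an unreconciled definition of the target effect. The aims and Statistical considerations state a loss from baseline; the Sample size section states a difference from LII. At the planned mean of 71.25 kg they coincide only under zero mean LII change, which the article neither states as an assumption nor justifies. A larger intervention loss, or a gain in LII, would preserve or widen the difference.

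On the article's inputs, each 1 % of LII loss takes 0.75 kg off the difference and roughly 18 percentage points off the 65 v 65 power over the first 2 %; a 1 % gain adds about 15 points. These sizes depend on assumed LII changes, an intervention loss of exactly 5 % and no baseline adjustment. The need to restate the power does not depend on the LII assumption, since the described comparison gives about 65 % even at zero change.

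**What to change.** - In Statistical considerations and Statistical methods, define the primary effect as the difference between each intervention arm and LII in 6-month weight change, adjusted for baseline weight by the ANCOVA already listed. Use the same definition in Sample size.
- Keep 5 % from baseline as the counselling goal only, and say that a 5 % loss within an arm is not by itself evidence of efficacy.
- In Sample size, state that zero mean LII change is assumed, correct the power for the single-arm comparison, and show it over a range of LII changes in both directions. If the adjusted analysis is to carry the power, state the correlation assumed.

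The cost is wording and a recalculated power statement. No more patients are needed for this change. The downside is that the stated power becomes less favourable on the present unadjusted inputs.

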### Sample size

During 2012, 756 overweight or obese women (with a BMI comprising between 25 and 40 kg/m^2^) underwent surgery for early-stage (non-metastatic) breast cancer at the European Institute of Oncology. Data for these patients were retrieved from our institutional breast cancer patients’ database. The mean weight of these 756 patients was 75 kg and the standard deviation was 9.

The sample size calculation was based on a superiority design of any single intervention (DI, PAI, or PADI) compared to the control group (LII). A sample group of 65 patients (control group) and similar number in any of the three intervention groups (diet and/or exercise) for a total of 195 patients achieve 80 % power to detect a 5 % weight loss (3.75 kg) between the null hypothesis that both group means are 75 kg and the alternative hypothesis that the mean of any of the intervention group 2 is 71.25 after 6 months, with known group standard deviations of 9.0 and 9.0 and with a significance level (alpha) of 0.05 using a two-sided two-sample *t* test. We have foreseen a drop-out of 5 % over the first 6 months.

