**Methods/design:**

This is a four-arm randomized controlled trial. Patients will receive a 6-month intervention and be followed for a further 18 months. Intervention is designed to improve adherence to a healthy diet and/or to increase physical activity, taking advantage of a wrist-based activity monitor. Participants will be recruited among overweight or obese breast cancer patients treated at the European Institute of Oncology, after completion of eventual adjuvant chemotherapy and/or radiotherapy. It is envisaged that 260 patients will be randomized into four arms: Dietary Intervention; Physical Activity Intervention; Physical Activity and Dietary Intervention; and Less Intensive Intervention. Women will be offered individualized counseling consisting of face-to face discussion and phone calls in addition to group meetings. A motivational interviewing approach will be used to encourage health behavior change. All participants will be given a pedometer device to monitor their physical activity. Participants’ dietary intake will be repeatedly assessed using a validated food frequency questionnaire. Participants’ quality of life and anxiety will be assessed with the Functional Assessment of Cancer Therapy-Breast and the State-Trait Anxiety Inventory questionnaires. Blood samples will be collected at baseline and follow-up visits to assess lipid and hormone profiles. Body composition will be repeatedly assessed using bioelectrical impedance vector analysis for identifying changes of fat and fat-free mass. Women allocated to the less intensive intervention arm will be considered as the control group.

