### Study population and randomization

Potential study participants will be recruited among all overweight or obese breast cancer patients treated at the IEO after breast cancer treatments (surgery, chemotherapy and/or radiation therapy) have been completed. Women undergoing hormone therapy will be eligible for the study. Groups of eligible participants will be invited at IEO for further eligibility assessment and enrolment. On arrival, they will receive a progressive number from the front desk receptionist. After an information meeting, they will be invited to sign all the study documents (informed consent form, privacy disclosure). Height, weight, waist and hip circumferences, and body composition will be measured. Participants who are eligible will receive the study questionnaires to be filled in. They will then be called following their random arrival number and be allocated in a 1:1:1:1 ratio to one of the four intervention arms: Dietary Intervention (DI); Physical Activity Intervention (PAI); Physical Activity and Dietary Intervention (PADI); or Less Intensive Intervention (LII) following a pre-established randomization list (Fig. 1). The randomization list was created using a computer random number generator and securely kept by a study collaborator not involved at the front desk. Randomization is not stratified, but blocks of 20 were created to achieve balance in the allocation of participants to the four treatment arms. The randomization list is not known to the front desk receptionist (administrative staff) who provides the progressive number that will be matched with the randomization number at the end of the information meeting. Randomization will be made by a member of the InForma study team (dietician or physiotherapist). This to ensure that allocation cannot be guessed before registration. Allocation is fixed and cannot be changed after randomization.

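### The stated 80% power for any single intervention versus control does not follow from the stated inputs: 65 women per arm give about 65%, or about 63% after 5% drop-out

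*Protocol article*

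**What the plan says.** The Sample size section describes the calculation as resting on a "superiority design of any single intervention (DI, PAI, or PADI) compared to the control group (LII"), so the comparison is one intervention arm against one control arm. The numbers given are "A sample group of 65 patients (control group) and similar number in any of the three intervention groups", then "for a total of 195 patients achieve 80 % power to detect" a 5% weight loss, expressed as 3.75 kg (mean 75 kg under the null, 71.25 kg in the intervention group). The calculation is "with known group standard deviations of 9.0 and 9.0", two-sided alpha 0.05, by a two-sample t test. A 5% drop-out over the first 6 months is foreseen.

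The Abstract gives the total: "It is envisaged that 260 patients will be randomized into four arms". Under Study population and randomization, women will "be allocated in a 1:1:1:1 ratio to one of the four intervention arms". Hence there are 65 women per arm, and every single comparison with LII is 65 against 65.

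**The concern.** Two things in the paragraph do not fit together. First, an effect of 3.75/9.0, about 0.42 standard deviations, normally needs around 90 per group for 80% power at two-sided 5%, so 65 looks too few. Second, the text gives 195 as the total although 260 women are to be randomized. The number 195 is three arms of 65, that is, all intervention women together without the controls. This suggests that a calculation for the pooled interventions was written up as the calculation for each one.

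The single-arm comparisons are the reason given for the four-arm design. A reader who meets a non-significant result for one arm would, on the published figure, take the unadjusted test to have had a one in five chance of missing a 3.75 kg difference. On the stated inputs that chance is more than one in three.

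**Working it through.** **Inputs (all from the Sample size section unless noted).** Difference 3.75 kg (75 minus 71.25); SD 9.0 in both groups; two-sided alpha 0.05; two-sample t test; 65 per arm; drop-out 5%; equal allocation (Study population and randomization); 260 in total (Abstract).

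**Formula.** Power = P(|T| > t_crit), where T is non-central t with n1 + n2 − 2 degrees of freedom and non-centrality 3.75 / [9.0 × √(1/n1 + 1/n2)].

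**Step 1: the comparison as worded, 65 against 65.** The standard error is 9.0 × √(2/65) = 1.579 kg. The non-centrality is 3.75/1.579 = 2.375, and the critical value on 128 degrees of freedom is 1.979. Power is 65.5% (66.1% by the normal approximation). The stated 80% is not reproduced.

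**Step 2: after drop-out.** 65 × 0.95 = 61.75, about 62 per arm. The standard error is 9.0 × √(2/62) = 1.616 kg and the non-centrality is 2.320. Power is 63.4% (64.1% normal).

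**Step 3: other readings of the paragraph.**

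| Reading | Sizes | Power (t test) |
|---|---|---|
| Single arm against LII, one-sided | 65 v 65 | 76.4% |
| 195 as the whole sample | 65 v 130 | 77.9% |
| Three interventions pooled against LII | 65 v 195 | 82.6% |
| Pooled, after 5% drop-out | 62 v 185 | 80.7% |
| Pooled, smallest 1:3 size reaching 80% | 61 v 183 | 80.2% |

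The one-sided reading contradicts the stated two-sided test. The second reading is not a single-arm comparison and conflicts with 260 randomized. Only the pooled reading reaches 80%.

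**Step 4: where 65 and 195 probably come from.** The 1:3 calculation needs 61 controls. Inflated for drop-out, 61/0.95 = 64.2, rounded up to 65. Three times 65 is 195, and 65 + 195 = 260. All the published numbers are recovered, drop-out included.

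**Step 5: what the unadjusted pairwise test can detect.** At 80% power the detectable difference is 4.46 kg with 65 per arm (4.46/75 = 5.9%) and 4.56 kg with 62 per arm (4.56/75 = 6.1%). For this test only, 80% power at 3.75 kg would need 92 per arm.

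**Step 6: baseline-adjusted analysis.** Statistical methods lists analysis of covariance. Adjusting for baseline weight replaces 9.0 with 9.0 × √(1 − r²), where r is the correlation between baseline and 6-month weight. The article gives no r, so these are assumed values, at 62 per arm:

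| Assumed r | Residual SD (kg) | Power |
|---|---|---|
| 0.5 | 7.79 | 76% |
| 0.6 | 7.20 | 82% |
| 0.7 | 6.43 | 90% |

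**The case against.** The best defence is that the error lies in the description and not in the trial. SD 9.0 is the spread of body weight across women, whereas the outcome is weight change and Statistical methods lists analysis of covariance. For such an analysis 9.0 is a conservative input, and at a correlation of about 0.6 or more the single comparisons have 80% power with the women already planned. This stands. A reader might infer from the 65% that the trial is underpowered; the article does not show that. Equally, it does not make the published sentence true, because that sentence names an unadjusted t test with SD 9.0 and gives no correlation.

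A reader might also infer that the 5% drop-out was mentioned but never added, since four arms of 65 already make 260. That does not follow. If the pooled calculation is the source, 65 is already the inflated number.

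Finally, one might argue that 3.75 kg is too optimistic because LII women are not untreated: "They will receive general counseling on health to reduce weight", they receive two motivational calls, and all participants wear the activity monitor. The article gives no expected LII loss, and no mean change in controls is a legitimate planning assumption, openly stated as a control mean of 75 kg. The Background reports that most women gain weight during and after treatment, although enrolled women are more than 6 months past their main treatment. What remains is a matter of labelling: 5% is the within-arm goal elsewhere in the article, and it equals the between-arm difference only if LII does not change.

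**Conclusion.** The concern holds as an error in the stated power. On the article's own inputs, each single intervention against LII has about 65% power at 65 per arm and about 63% at 62 per arm, some 15 to 17 percentage points below the stated 80%. This conclusion needs no outside assumption. That the figures come from a pooled 1:3 calculation is an inference, but it recovers 61, 65, 195 and 260 exactly and no other reading tried does. The power of the trial under its likely adjusted analysis is not established either way; it depends on a correlation that the article does not give.

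**What to change.** Keep 260 women and rewrite the Sample size paragraph:

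1. State that each pairwise unadjusted t test has about 63% power for a 3.75 kg difference from LII with 62 evaluable women per arm, and a detectable difference of about 4.6 kg at 80% power. Say that 80% applies only to the three interventions pooled against LII.
2. Label 195 as the three intervention arms together and 260 as the total randomized.
3. Describe 3.75 kg as a between-arm difference that assumes no mean weight change in LII.
4. Give the power of the baseline-adjusted analysis of covariance together with its assumed baseline-to-6-month correlation, for example about 76%, 82% and 90% at correlations of 0.5, 0.6 and 0.7 with 62 per arm. Without this, the 63% alone would give too pessimistic a picture if the adjusted analysis is the one used.

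The cost is a rewording and a less favourable unadjusted figure. Enrolment, arms and analysis do not change.
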